## Abstract

**Background:**

Due to improvements in cancer survival the number of people of working age living with cancer across Europe is likely to increase. UK governments have made commitments to reduce the number of working days lost to ill-health and to improve access to vocational rehabilitation (VR) services. Return to work for people with cancer has been identified as a priority. However, there are few services to support people to remain in or return to work after cancer and no associated trials to assess their impact. A pilot randomised controlled trial among women with breast cancer has been designed to assess the feasibility of a larger definitive trial of VR services for people with cancer.

**Discussion:**

To our knowledge this is the first study to determine the feasibility of a randomised controlled trial of the effectiveness of VR services to enable people with cancer to remain in or return to employment. The study will provide evidence to assess the relevance and feasibility of a larger future trial involving patients with breast, prostate or lung cancer and inform the development of appropriate VR services for people living with cancer.

**Trial Registration:**

ISRCTN: ISRCTN29666484

Registration date: 07/10/10; Randomisation of first patient: 03/12/10

## 1 Background

Due to improvements in cancer survival the number of people of working age living with cancer across Europe is likely to increase [1]. It is estimated that more than 500,000 people in the UK under the age of 65 years have been diagnosed with cancer during their working lives [2]. Every year in Scotland around 27,400 people are diagnosed with cancer, 52% (n = 14,300) of whom are women [3]. Breast cancer is the most commonly diagnosed cancer in Scottish women and incidence has increased by 8% over the past decade attributed, in part, to earlier detection due to mammography screening programmes[3]. In 2007 over half (55%) of all women diagnosed with breast cancer in Scotland were of working age (i.e., between 18 and 65 years): around 1 in 20 were under 40 years, and 1 in 5 were under 50 years [4]. Despite notable variation across countries, [5] breast cancer mortality rates are decreasing across Europe[6,7]. In a recent comparative analysis of 30 European countries, England and Wales, Scotland, and Northern Ireland had the second, fourth and fifth largest overall decline in mortality between 1989 and 2006 of 35%, 30% and 29%, respectively [5]. There is evidence that the trends of increasing incidence [8] and decreasing mortality will continue [5]. Remaining in or returning to work will therefore be increasingly important for women living with breast cancer in Scotland and across the UK and Europe.

Dame Carol Black's recent review of the health of Britain's working age population recommended a multi-agency and partnership approach to supporting people to remain in or return to work and highlighted the role of line managers, general practitioners (GP) and vocational rehabilitation (VR) services[9]. UK governments have made commitments to reduce the number of working days lost to ill-health and to improve access to VR services. In Scotland, the Scottish Centre for Healthy Working Lives (SCHWL) has established pilot VR services in National Health Service (NHS) Tayside and NHS Lothian. These services support people to remain in or return to work by providing fast-track care and services such as physiotherapy, counselling and occupational therapy to employees from small- to medium-sized companies with less than 250 employees, where occupational health support services are not available. The Scottish Government has recently identified return to work for people living with cancer as a priority [10].

People with cancer can often experience changed workplace relations or employment status following diagnosis or during treatment, with negative financial and psychosocial consequences. It is known that individuals change jobs, leave paid employment or experience a decline in earnings [11]. Individuals may also experience discrimination from employers or colleagues [11]. However, a recent review has identified that there are few services to support people to remain in or return to work after cancer and no associated trials to assess their impact [11].

The SCHWL and Macmillan Cancer Support are developing plans to expand VR services to people with cancer. The establishment of pilot VR services across Scotland may provide an opportunity to conduct a large randomised controlled trial to evaluate their effectiveness for people living with cancer. However, there are several uncertainties that must be addressed including an assessment of the feasibility of such a trial and the acceptability of the intervention among people with cancer. Given increasing incidence and survival of people living with breast cancer, it is both timely and appropriate to determine the feasibility of this definitive trial through a pilot randomised controlled trial (RCT) of VR services among women following surgery for breast cancer. A study design incorporating a pilot RCT was selected to refine, and assess the feasibility of, trial processes (including, recruitment, randomisation and follow-up) and estimate the likely effect size in advance of a larger, more definitive, future trial.

## 2 Aim

The aim of this study is to determine the feasibility of an RCT of VR services among women with breast cancer following surgery and whether this intervention is acceptable in this patient group.

### 2.1 Objectives

1. Determine the numbers of patients in Lothian and Tayside with breast cancer referred for surgery who are in paid or self-employment and potentially eligible for the RCT.

2. Assess whether it is feasible and acceptable to recruit patients into the trial post-operatively. If not, identify the most appropriate timing for recruitment and the employment intervention that follows.

3. Estimate trial recruitment rates (i.e., percentage of eligible women who consent to the trial) and attrition over the period of the trial.

4. Determine whether the outcomes are measurable and appropriate, and evaluate the instruments used to measure secondary outcomes (i.e., FACT-B, FACIT-Fatigue).

5. Estimate the likely effect size to inform the power calculation for a larger, more definitive trial.

6. Assess the feasibility of including patients with lung and prostate cancer in a larger future RCT.

## 3 Methods

### 3.1 Design

The design of this feasibility study is an interventional two-arm RCT (Figure 1).

**Figure 1 F1:**
[figure not shown]
Study Design Flowchart: enrolment, randomisation and follow-up

### 3.2 Setting and participants

Patients with breast cancer are being recruited from three hospitals in two NHS Boards in Scotland (Perth Royal Infirmary (PRI), and Ninewells Hospital, Dundee [NHS Tayside]; Western General Hospital (WGH), Edinburgh [NHS Lothian]). Recruitment to the trial is proceeding for 6 months at each site.

#### 3.2.1 Eligibility

Eligible patients are all women who are: (1) aged between 18 and 65 years; (2) in paid employment or self-employed; (3) living or working in Lothian or Tayside, Scotland, UK; (4) diagnosed with an invasive breast cancer tumour; (5) treated first with surgery. Patients diagnosed with Ductal Carcinoma in Situ (DCIS) are excluded. Patients are not excluded on the basis of communication difficulties. Interpretation and translation services will be used for participants unable to communicate in English. Patients with learning difficulties are also not excluded as a study investigator (GH) has expertise involving people with learning difficulties in research.

#### 3.2.2 Sample size calculation

There are several uncertainties that this feasibility study seeks to address before a larger, more definitive RCT of vocational rehabilitation services for people with cancer can be conducted. These uncertainties include: (1) the number of women who may be eligible for inclusion in the trial; (2) the percentage of eligible women who meet the VR services' criteria for referral; (3) the recruitment rate, defined as the percentage of eligible women who consent to involvement in the trial. The feasibility study will therefore provide evidence to inform sample size calculations for a larger trial. However, we estimate that between 66 and 79 patients will be recruited to the feasibility study over a 6 month period. This sample size is based on diagnosis and surgical data obtained from 2008, estimated employment rates, and a conservative recruitment rate of between 50% and 60%.

The feasibility study is also assessing the likely effect size to inform sample size calculations for a potential larger future trial. The primary outcome measure is the number of days off work in the 6 months following surgery. One report indicated that the mean length of time absent from work after a diagnosis of breast cancer was 5.6 months [12]. Assuming, therefore, a mean of 180 days absent from work in the control group and an estimated standard deviation of 100 days, with a sample size of 70 (35 in each group), the study would be able to detect a reduction in number of days absent from work from 180 to 110 days with 5% level of significance and 80% power. A larger sample size would be required to detect smaller differences. To detect a reduction in number of days absence by 2 months, a sample size of 88 patients (44 in each group) would be required. To detect a reduction of 1 month, a sample size of 350 (175 in each group) would be required.

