### 3.6 Data collection

Data to evaluate the intervention in terms of quality of life, fatigue and change in employment status are collected at baseline, 6 months and 12 months after entry to the trial via a self-completion questionnaire. In addition, self-reported sickness absence is collected every four weeks for the first 6 months of follow-up and for the four weeks before the 12-month follow-up time point (Figure 1). A telephone reminder is administered if questionnaires are not returned within 10 days. Participants have the option of a researcher collecting their responses to all questionnaires by telephone.

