### 3.7 Outcome measures

#### 3.7.1 Primary outcome

The primary outcome measure is self-reported number of days off work due to ill-health within the first six months after surgery.

There are two main ways of measuring absence from work: (1) sick leave register at participants' place of employment; (2) participant self-report. Although a sick leave register managed by the employer is regarded as the gold standard, self-report is also robust [17]. One study found more than 96% accuracy between register and self-report when the recall period is limited to 2 to 4 weeks [18]. The feasibility of using sick leave registers will be determined by asking participants to consent to contact with their employers to access their sick leave register at the end of the 6 month follow-up period.

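### The assumed control mean of 180 days with SD 100 days cannot occur for days off work counted within six months, so the stated power and the sizes 88 and 350 do not describe this outcome

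*Protocol article*

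**What the plan says.** Section 3.2.2 of the protocol article defines the outcome used for sizing: "The primary outcome measure is the number of days off work in the 6 months following surgery". Section 3.7.1 says the same: "The primary outcome measure is self-reported number of days off work due to ill-health within the first six months after surgery". Section 3.6 collects it over that window: "self-reported sickness absence is collected every four weeks for the first 6 months of follow-up".

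The control mean is taken from a cited report: "One report indicated that the mean length of time absent from work after a diagnosis of breast cancer was 5.6 months". The calculation then starts from these inputs: "Assuming, therefore, a mean of 180 days absent from work in the control group and an estimated standard deviation of 100 days". No source is given for the SD.

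Three results follow in section 3.2.2:
- 35 per group is said to give 80% power at the 5% level for a fall from 180 to 110 days.
- A two-month reduction is said to need 88 patients (44 per group).
- For the smallest effect: "To detect a reduction of 1 month, a sample size of 350 (175 in each group) would be required".

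The same section derives the expected recruitment of 66 to 79 separately, from 2008 diagnosis and surgery data, employment rates and a 50% to 60% recruitment rate.

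**The concern.** A count of days inside a six-month window has a hard upper limit. A mean of 180 puts the average control patient almost at that limit, which leaves almost no room for spread, yet the assumed SD is more than half the width of the whole range. The mean and SD look like values for total length of absence, carried over to an outcome that stops at six months.

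At stake is whether the paragraph describes the trial. The power statement, 88 and 350 all rest on the SD of 100. Objective 5 in section 2.1 is to estimate an effect size for the power calculation of a larger trial, so a reader planning that trial may pick up the SD and the two sizes. The ceiling also bears on objective 4, which asks whether the outcomes are measurable and appropriate. If many patients in both arms are off work for the whole window, the outcome cannot separate them.

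**Working it through.** **Inputs.** From section 3.2.2: control mean 180, SD 100, differences of 70 days, 2 months and 1 month, 5% significance, 80% power. From section 3.8.1: independent samples t-test. Assumed here: two-sided test, 2 months = 60 days, 1 month = 30 days, six months = 181 to 184 calendar days (182 where one value is needed).

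**1. Reproduce the plan's figures.** Per-group size is n = 2(1.960 + 0.842)² × (SD/d)² = 15.70 × (SD/d)². With SD 100:
- d = 30: 15.70 × 11.11 = 174.4, so 175 per group, 350 in total. Exact.
- d = 60: 15.70 × 2.778 = 43.6, so 44 per group, 88 in total. Exact.
- d = 70: 15.70 × 2.041 = 32.04, so 33 per group, 66 in total (68 by the t-test), against 70 stated. With 35 per group, power is 83.4% (normal) or 82.3% (t-test).

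The calculation is sound, given its inputs.

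**2. Are the inputs possible?** For any variable between 0 and M with mean m, SD ≤ √(m(M − m)), and never more than M/2. This needs no distributional assumption.

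| M (days) | Largest SD at mean 180 | Largest SD at any mean |
|---|---|---|
| 181 | √(180 × 1) = 13.4 | 90.5 |
| 182 | √(180 × 2) = 19.0 | 91.0 |
| 184 | √(180 × 4) = 26.8 | 92.0 |

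An SD of 100 is ruled out at every mean. With a mean of 180 it would need values up to at least 180 + 100²/180 = 235.6 days. Reading the four-weekly reports as seven periods (196 days) does not help: the limits become 53.7 and 98. With six periods (168 days) the mean of 180 is itself out of range.

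**3. Fixed difference inside the window, at the largest possible SD (91).**
- 70 days: 15.70 × (91/70)² = 26.5, so 27 per group, 54 in total. With 35 per group, t-test power is 88.7%.
- 60 days: 36.1, so 37 per group, 74 in total.
- 30 days: 144.4, so 145 per group, 290 in total.

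If each arm takes the largest SD for its own mean (19.0 at 180 and 89.0 at 110, root mean square 64.3), power for 70 days with 35 per group is 99.4%.

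The detectable difference with 33 to 39 per group (66 to 79 patients in equal arms, t-test, 80% power) is 63.7 to 58.5 days at SD 91. At an illustrative SD of 50 it is 35.0 to 32.1 days.

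**4. If the reductions mean total absence.** Illustration only: total absence with mean 170 to 180 and SD 100 (gamma, lognormal or normal), cut off at 0 and 182 days, 2 million simulated values per case.
- Controls in the window: mean 136 to 144, SD 41 to 57, with 34% to 49% at the ceiling.
- A 30-day cut in total absence appears as about 11 to 21 days in the window, and a 60-day cut as about 28 to 44. The range depends on the distribution and on whether the cut is a fixed shift or proportional.
- At SD 50, 21 days needs 15.70 × (50/21)² = 89.0, so 89 per group (178 in total). 11 days needs 15.70 × (50/11)² = 324.3, so 325 per group (650 in total). The stated 350 lies inside this range.

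**The case against.** The strongest reply is that little depends on these inputs. The arithmetic is right, the expected 66 to 79 patients come from accrual, the aim is feasibility and acceptability, and section 3.8 says that hypothesis testing must be cautious. Section 3.2.2 also says that the pilot will supply the evidence for sizing the larger trial. All of this stands, and it limits the consequences. It does not make the inputs possible, and a power statement built on them is still wrong as written.

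Some stronger readings are tempting, but the documents do not support them:
- *The trial is underpowered.* For the plan's own 70-day difference inside the window, an SD of 100 understates power.
- *The one-month size should be 88, not 350.* At SD 50 a full 30-day in-window difference does need 15.70 × (50/30)² = 43.6, so 44 per group (88 in total). That caps the SD but not the effect, and step 4 shows that the effect may shrink too.
- *88 and 350 are the definitive trial's planned sizes.* The protocol presents them only as what smaller differences would need, and 70 is the size assumed for this study.
- *The cited 5.6 months is known to be uncapped.* The protocol states no cap, but the report is not available here. The point does not depend on it.

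**Conclusion.** The point holds as an infeasible input, not as a calculation error. With the outcome confined to six months, the SD cannot exceed about 92 days at any mean, or about 13 to 27 days at a mean of 180. A mean of 180 with SD 100 therefore cannot occur, and nothing else in the protocol rescues it. The 80% power for 180 versus 110 days, and the sizes 88 and 350, are not properties of this outcome.

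The direction of the error depends on what a reduction means. For a fixed in-window difference the plan overstates the numbers: at most about 290 in total for 30 days, against 350. For a reduction in total absence the ceiling dilutes the effect, and the required size could be below or above 350.

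The bound on the SD rests only on counting calendar days over six months. The figures at SD 50 and those from the capped distributions rest on assumed values and are illustrative. The pilot's recruitment target is unaffected.

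**What to change.** Rewrite the second paragraph of section 3.2.2 on the six-month scale:
- Give a control mean below the ceiling, a range of SDs within the feasible bound (labelled as an assumption) and the expected share of patients off work for the whole window.
- Recompute the difference that 66 to 79 patients can detect over that SD range.
- Recompute or withdraw 88 and 350. For each reduction, say whether it is measured within the window or in total absence; if total, state the in-window difference it is expected to produce. Label any alternative sizes as illustrative.
- State that the pilot will estimate the in-window SD and the share at the ceiling in each arm, for use in sizing the definitive trial.

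The cost is one rewritten paragraph and a short recalculation. No more patients, visits or data are needed, since the four-weekly absence reports already supply both quantities.

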### 3.3 Patient Recruitment

Recruitment and obtaining written informed consent to be involved in the study is occurring before participants are randomly assigned to the intervention or usual care arm of the study. Breast care nurses are initially applying the inclusion criteria to patients attending hospital in the pre-operative phase. Due to variation in local clinical processes, service size and workforce capacity the recruitment process differs in each of the three hospitals.

#### 3.3.1 Perth Royal Infirmary (PRI)

Women who are eligible for inclusion in the RCT are identified from surgical lists by clinical teams. Eligible women are given information about the study by their breast care nurse at a pre-operative appointment. Written informed consent is taken at a face-to-face meeting with a researcher (RGK) when women attend hospital for a post-operative clinic appointment.

#### 3.3.2 Ninewells Hospital, Dundee

Eligible women are identified from surgical lists by clinical teams and are given a pack of information about the study when they attend hospital for surgery. Women return this information pack to their breast care nurse when they leave hospital the following day or by post to a researcher (RGK). Those who agree to participate include their written informed consent in their returned pack.

#### 3.3.3 Western General Hospital (WGH), Edinburgh

Eligible women are identified by clinical teams from staging information discussed at a weekly multi-disciplinary team meeting. Eligible women are given a pack of study information by their breast care nurse when they attend hospital for a pre-operative appointment and return this to their breast care nurse when they attend for surgery or by post to a researcher (RGK). Those who agree to take part in the trial include their written informed consent in the returned information pack.

In each hospital, patients who do not want to participate are asked if they consent to the retention of a limited set of anonymised clinical, sociodemographic and employment data (e.g., age, sex, postcode, diagnosis, treatment, employment status) so that a comparison can be made between patients who do and do not agree to be approached (Figure 1). Data are recorded on the number of patients who are eligible and reasons for ineligibility, the numbers who consent to participate in the trial and the numbers who consent to retention of anonymised data.

### 3.4 Randomisation

The allocation sequence was generated from a Bernoulli probability distribution with a specified probability of 0.5 which ensures participants have an equal chance of being in either group. Participants are randomly assigned to the intervention and usual care arm with a 1:1 allocation ratio (Figure 1). A separate sequence is used for each NHS Board (analogous to the VR service to which participants in the intervention arm are referred) to ensure that there is an even distribution of participants to the intervention and usual care groups in each NHS Board. The allocation sequences are concealed from the researchers responsible for recruiting patients into the trial (RGK), data collection (RGK) and data analysis (RGK, JE, NMG, GH). The trial statistician (DA) provided the allocation sequences to an administrator in the Cancer Care Research Centre at the University of Stirling who is not involved in the process of random number generation nor data collection and analysis. This individual will assign patients to the intervention and usual care groups and refer patients in the intervention arm to the VR service.

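### Separate unrestricted Bernoulli(0.5) lists per NHS Board cannot ensure the even arm distribution that the protocol claims for them

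*Protocol article*

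**What the plan says.** Section 3.4 (Randomisation) of the protocol article gives the method: "The allocation sequence was generated from a Bernoulli probability distribution with a specified probability of 0.5". It says of this method, correctly, "which ensures participants have an equal chance of being in either group". It then gives the ratio: "Participants are randomly assigned to the intervention and usual care arm with a 1:1 allocation ratio".

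Next comes the stratification: "A separate sequence is used for each NHS Board", which the text equates with the VR service to which intervention women are referred. The stated purpose is "to ensure that there is an even distribution of participants to the intervention and usual care groups in each NHS Board". The article describes no blocking, urn scheme, minimisation or other restriction.

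Section 3.2.2 (Sample size calculation) states: "we estimate that between 66 and 79 patients will be recruited to the feasibility study over a 6 month period". Its power statement is made "with a sample size of 70 (35 in each group"). Section 3.2 (Setting and participants) names three hospitals in two Boards and does not say how many women each Board is expected to supply.

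**The concern.** The property claimed is not one that the described method has. Bernoulli sampling fixes the probability for each woman; it does not fix or bound the number per arm. Two unrestricted lists, one per Board, produce exactly the same distribution of arm counts by Board as a single unrestricted list, so the separate sequences do nothing towards the purpose given for them.

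Three features of this trial make that worth correcting:

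- Board is the VR service, and it is the factor that the authors themselves chose to balance.
- The primary analysis in section 3.8.1 is an independent samples t-test with no Board term stated. A chance difference in Board mix between arms would therefore pass unadjusted into the estimated effect, which objective 5 uses to power the definitive trial.
- Section 1 lists randomisation among the processes that the pilot is meant to refine and assess. A scheme wrongly believed to guarantee balance could be carried into the larger trial.

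**Working it through.** **Inputs.** From the protocol article: allocation probability 0.5 and two Boards (sections 3.4 and 3.2); 70 women at 35 per group, 180 versus 110 days, SD 100 days, 5% significance and 80% power (section 3.2.2). Assumed: independent draws (the ordinary reading of a Bernoulli sequence), a two-sided test, and Board sizes of 20, 35 and 50 to cover a range, because the article gives none.

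**1. The plan's own figure.** The normal-approximation formula is n per group = 2(1.96 + 0.842)² × SD² / difference². For 70 days this is 2 × 7.85 × 10,000 / 4,900 ≈ 32.0, or 33 after rounding up. The noncentral t calculation needs 34. The same normal formula gives 44 for 60 days and 175 for 30 days, both as stated. The planned 35 per group is thus reproduced to within two women and has t-test power of 0.823.

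**2. Arm counts under the stated method.** In a Board of n women the intervention count is Binomial(n, 0.5), and the difference between arms has SD √n. The two-sided probability is P(larger arm ≥ 0.6n) = 2 × P(X ≤ 0.4n). The one-sided probability, for a shortfall in the intervention arm only, is half of that.

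| Assumed Board size | SD of arm difference | Central 95% range for one arm | 60:40 or worse, either direction | Intervention arm at 40% or less |
|---|---|---|---|---|
| 20 | 4.5 | 6 to 14 | 0.503 | 0.252 (8 or fewer) |
| 35 | 5.9 | 12 to 23 | 0.311 | 0.155 (14 or fewer) |
| 50 | 7.1 | 18 to 32 | 0.203 | 0.101 (20 or fewer) |

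**3. Both Boards together.** P(at least one Board at 60:40 or worse) = 1 − (1 − p₁)(1 − p₂). For 35 and 35 women: 1 − 0.689² ≈ 0.52. For 20 and 50: 1 − 0.497 × 0.797 ≈ 0.60. Under either split, a visible imbalance in some Board is more likely than not.

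**4. Effect on overall power.** At a total of 70, a 42:28 split or worse in either direction has probability 0.120. The noncentrality is 0.7 / √(1/n₁ + 1/n₂). At 35:35 it is 2.93, with power 0.823; at 28:42 it is 2.87, with power 0.807. The loss is 1.6 percentage points.

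**5. Comparison with a restricted scheme.** With permuted blocks of 4 and 6, the arm difference within a Board can never exceed half of the largest block, which is 3. Under the Bernoulli lists, a difference of 4 or more has probability 0.50 at n = 20, 0.50 at n = 35 and 0.67 at n = 50.

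**The case against.** Simple randomisation is a valid and unbiased method. Any imbalance by Board is a chance event and not systematic confounding, and its price in overall power is 1 to 2 points. This stands, and it limits the point to a mismatch between method and stated purpose.

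A reader might infer that the plan also promises a 35:35 split, which has probability only 0.095 at a total of 70. The document does not support that: 35 per group is an assumption inside a power statement, and the same section expects 66 to 79 women.

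A reader might also infer that a VR service is likely to be left with too few intervention women. Only a shortfall in that arm would cause this, so the one-sided column applies. The article sets no minimum per service, none of the six objectives in section 2.1 is a judgement service by service, and section 3.5 gathers service information only as context for possible differences.

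Balancing by Board would not balance hospital or recruitment route: Tayside contains Perth and Ninewells, where consent is taken in different ways (sections 3.3.1 and 3.3.2).

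Finally, randomisation began on 03/12/10 and recruitment lasts six months per site. New lists cannot undo imbalance already accrued, and blocks are more predictable than unrestricted lists when patients know their arm. That bears on which remedy to choose; it does not rescue the claim. The article is condensed and the full protocol may describe a restriction; if so, section 3.4 misdescribes the scheme and still needs correcting.

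**Conclusion.** Section 3.4 is wrong as written: the lists it describes give equal chance, not even numbers within Board. The conclusion does not depend on the assumed Board sizes; only the magnitude does. Across Boards of 20 to 50 women, a 60:40 or worse split has a probability of about 50% down to 20%, and a shortfall of that size in the intervention arm about 25% down to 10%.

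The figures rest on independent draws with no unreported restriction. The documents do not support reading this as biased allocation, a material loss of power or a broken promise of 35 per group. The loss is control over Board, the authors' own balancing factor, together with a claim that readers and the planners of the larger trial could rely on by mistake. It should be corrected; it does not invalidate the trial.

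**What to change.** **If a useful number of women remain to be allocated:** use randomly permuted blocks of varying size (for example 4 and 6) within each Board for those women. The trial statistician generates the lists, the existing independent administrator holds them, and block sizes stay hidden from recruiting staff. The limit of 3 on the arm difference then applies to the women allocated under the new lists, and the change of scheme should be reported. The cost is one new list per Board, a short amendment and slightly more predictable allocation, which the varying sizes and the existing central concealment limit.

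**If the lists are kept, or recruitment is too advanced:** delete the statement that evenness within Board is ensured, and describe the scheme as simple randomisation with a separate list per Board. This costs one sentence.

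**If a restriction was in fact used:** state it in section 3.4 in place of the Bernoulli description.
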